### Previous work

In previous work, [44] participants in the Healthy Nevada Project completed EHL and readiness to change surveys before (*n* = 424) and after (*n *= 174) an EDC exposure report-back intervention (measured via the MM mail-in testing kit). Report-back of results included urinary levels, information about health effects, sources of exposure, and personalized recommendations to reduce exposure. Participants ranged in age from 18-61, were primarily women (75%), and white (79%). EHL was generally very high at baseline. Higher EHL knowledge was shown among older participants (*p* = 0.02) and those self-rated in poorer health (*p *= 0.007). EHL behaviors increased after report-back (*p *= 0.003).

For readiness to change, 72% were already or planning to change their behaviors. Women were generally in earlier stages than men (p=0.071), but post-intervention, women increased their readiness (p=0.053), while men decreased (p=0.007). When asked what challenges they faced in reducing exposure, 79% cited not knowing what to do. This dropped to 35% after report-back. Participants with higher propylparaben were younger (p=0.03), women and participants who rated themselves in better health had higher levels of some phthalates (p=0.02-0.003 and p=0.001-0.003 respectively). After report-back, monobutyl phthalate decreased among the 55 participants who submitted a second urine test (p<0.001). Of the 50 participants who completed final surveys, 50% reported now using non-toxic personal products, 44% were using non-toxic household products, 20% dined out less, 32% ate less packaged food, 40% used less plastic, and 48% read product labels more.

The report-back intervention was successful as evidenced by increased EHL behaviors, increased readiness to change among women, a 44% reduction in the percentage of participants not knowing how to decrease exposure, a high percentage of participants reporting behavior changes to reduce exposure, and a decrease in monobutyl phthalate. An EHL questionnaire more sensitive to chemical exposures would help differentiate high and low literacy. Therefore, in the current study, a more sensitive EDC EHL survey will be employed. And although we observed improvements in EHL and RtC after report-back, more intensive EHL education could further improve knowledge and behavior, leading to reductions in EDC exposure. Thus, in this proposal, we aim to test our newly developed EDC EHL curriculum to encourage even more EDC reduction and EHL improvement.

### EDCs and clinical biomarkers

In addition to behavioral changes of individuals and measured exposure metabolite changes, we will also test a subset of study participants for changes in clinical biomarkers that could indicate improved health. EDCs have been shown to be linked to many adverse health outcomes, including cardiovascular and metabolic disease, diabetes, low hormone levels/hormone imbalance (including thyroid problems), infertility, cancers, and inflammation [16, 45]. However, the lack of health/clinical biomarker assessments for EDC-intervention studies is a major data gap in an already limited research area. This is also reflected in our recent customer discovery interviews with physicians/clinics, employee wellness programs, and major insurers. These stakeholders require information on the changes to known clinical biomarkers (i.e. a demonstration of the effectiveness of our testing and education intervention program) in order to acquire and market our service. Showing that our intervention to reduce EDC exposures can improve clinical biomarkers will significantly increase our products’ market value and commercialization potential as well as pave the way for FDA approval and insurance/health savings account coverage for individuals.

### Report-back and curriculum

Numerous studies have demonstrated that avoidance and lifestyle behavioral change are the most effective ways to reduce EDCs, particularly non-persistent EDCs such as BPA, phthalates, and parabens [46]. For example, reducing canned food/drink consumption and avoiding touching receipts are associated with reduced BPA and BPA alternatives exposures, and using fragrance-free personal care products is associated with lower phthalate exposure [46, 47]. Such evidence-based behavioral modification strategies have been developed and provided to our Phase I participants and regular Million Marker customers in their personalized Detect
& Detox Kit reports [48]. Despite this effort, we learned in Phase I that participants required more education, support, and “handholding.” In a 2022 review [47] on interventions on reducing exposure to EDCs in human health care context, the authors only found 12 intervention studies between 2011-2022 globally, with sample sizes ranging from 20-218 participants and intervention durations of 3 days to 6 months. Unlike our Phase I study, none of the studies provided report-back to the participants. We have also recruited over 400 participants, which made us the largest intervention study to date. The authors pointed out that only four studies provided their participants with education and four let their participants choose alternative goods or foods themselves, which suggested the lack of self-directed behavior change and real-world application and generalizability. Most of the studies intervened in one aspect (i.e., dietary modification vs. using alternative household or personal care products) of participants’ lifestyle behavior rather than all potential sources of EDCs, and it was unclear whether the short-term behavior changes could be sustained over a long period of time or throughout the life course. Lastly, the review indicated the need for randomized controlled trials and participant-centered studies promoting active participation and practices. Therefore, insights derived from previous research and recommendations from the latest scientific publications indicate the need to enhance our existing service with a participant-driven education behavioral intervention program that builds behavioral change knowledge and skills that we can put to test through a randomized longitudinal study.

Sustained lifestyle and health behavioral change requires knowledge and skills that are based on the science of behavior change [49]. Behavioral counseling programs with consistent, regular interaction with a health coach combined with education, support and skill building have been proven effective for reducing chronic disease risks [50]. Given the success of the DPP and Omada Health (digitization of the DPP) in achieving behavioral and clinical outcome goals, as well as their proven framework of translatability (including training, intervention delivery, support and evaluation) [51] and business model, it is prudent to model our education behavioral intervention program after DPP and Omada Health.

The DPP has proven to be highly effective at curbing diabetes through achieving lifestyle goals of a minimum 7% weight loss/weight maintenance and a minimum of 150 minutes of physical activity similar in intensity to brisk walking [52]. The success of DPP was attributed to other key features, including 1) individual lifestyle coaches; 2) frequent contact with participants; 3) a structured 16-session core-curriculum that taught behavioral self-management strategies for weight loss and physical activity; 4) physical activity sessions; 5) flexible maintenance intervention combining group and individual approaches and motivational campaigns; 6) individualization through a diabetes toolbox of adherence strategies; 7) tailoring of materials and strategies to address ethnic diversity, and 8) an extensive network of training, feedback, and clinical support [52].

Given the flexibility, accessibility, convenience, and scalability of digital health and mobile interventions, [50, 53] Omada Health pioneered the translation of DPP into digital format and demonstrated its long-term effectiveness [54]. The Omada’s program consists of a weekly interactive behavior change curriculum focused on weight loss and physical activity, digital tracking tools, personalized health coaching, and online small group support. The lessons include reading content, interactive games or exercise, and written reflections and goal-setting activities [50].

Leveraging the insights, key ingredients and program structure of DPP and Omada’s digital DPP program, our self-directed online interactive education curriculum will consist of the following 1) evidence-based 8-lesson curriculum covering topics related to EDCs (basic science of EDCs, health impact, exposure sources, etc.), see details in Table 1; 2) take-home handouts, practical tip sheets and checklists to facilitate behavior reinforcement; 3) live coaching sessions at the end of each lesson; 4) individualized support through online messaging, text messaging, phone and video calls; 5) community support through an online forum, and 6) personalized exposure biomarker testing and report-back with tailored behavioral and product recommendations. We will put strong emphasis on what people can control and small steps to reduce harmful exposures. Our curriculum and interventions will be grounded in social cognition theory, where behavioral change begins with individuals’ perception of their behavior on health, [55] as well as Theory of Planned Behavior, where we will promote a sense of self-efficacy and utilize techniques such as goal setting, feedback, self-regulation and social support to achieve and sustain EDC-reduction behaviors [56–58].

**Table 1 Tab1:** Example topics covered in Million Marker’s 8-lesson curriculum

Class	Topics Covered	Description
1	Course orientation, introduction to environmental health and EDCs	● Overview of the endocrine system ● Overview of environmental health and EDCs ● Persistent vs. transient chemicals ● Acute vs. chronic exposures ● Chemical absorption, metabolism, distribution and excretion ● EDCs and fertility, fetus/child development ● **Reflective journal promp**t: take a look around your room and determine some primary EDC exposures
2	Chemicals in personal care products, beauty products, cosmetics	● Soap, hair care, skin care, oral care ● Feminine hygiene and intimate products ● Fragrance/perfume/parfum, makeups ● How to read ingredient labels ● **Reflective journal prompt:** what’s on your plan of action to reduce EDC exposures?
3	Exposures from kitchen, bedroom, living room, bathroom	● Kitchen: dish detergent, all-purpose cleaners, sponge, wipes/antibacterial products ● Living rooms/bedrooms: scented plug-ins/candles/air fresheners, dust/mold ● Bathroom: shower curtain, toilet cleaner, mold/mildew cleaner ● **Reflective journal prompt**: what are some cleaning products that you need or don’t need?
4	Exposures around the house and the house itself	● Textiles: clothing, bedding, rugs ● Furniture, floors ● **Reflective journal prompt**: what are some upcoming big-ticket purchases? What would you consider when making such purchases?
5	Exposures from food, water, and medications	● Contamination and exposures in food ● Water: municipal water and well water, water testing, water filters ● Supplements/medications: capsule coating, medical supplies and dental sealants ● **Reflective journal prompt**: How many foods that you eat in a day that are processed vs whole foods?
6	Shopping for, cooking, and ordering Foods	● How to read ingredient labels ● How to shop ● Food packaging, cookware, food storage ● **Reflective journal prompt**: How often do you cook at home?
7	Clothing, electronics, and cars	● Jewelry, clothing, and bedding ● Researching clothing ● Electronics, cars, and hobbies ● **Reflective journal prompt**: what are ways you can reduce your exposures that require some planning?
8	Course wrap-up and review	● Course review and highlight major takeaways ● **Reflective journal prompt**- do you have any plans for the next 6 months? 12 months?

**Table 2 Tab2:** SPIRIT Guideline Checklist

Section/Item	Reporting Item	Description	Page and Line Number	Reason if not applicable
Title	#1	Descriptive title identifying the study design, population, interventions, and, if applicable, trial acronym	p. 1, 1-3	
Trial registration	#2a	Trial identifier and registry name. If not yet registered, name of intended registry	Clinical Trials, NCT06450951 (https://www.clinicaltrials.gov/)	
Trial registration: data set	#2b	All items from the World Health Organization Trial Registration Data Set	All items included in the Methods and Intervention, p. 9-21	
Protocol version	#3	Date and version identifier	p. 23, 545-547	
Funding	#4	Sources and types of financial, material, and other support	p. 26, 612-615	
Roles and responsibilities: contributorship	#5a	Names, affiliations, and roles of protocol contributors	p. 26, 617-621	
Roles and responsibilities: sponsor contact information	#5b	Name and contact information for the trial sponsor	p. 1, 11	
Roles and responsibilities: sponsor and funder	#5c	Role of study sponsor and funders, if any, in study design; collection, management, analysis, and interpretation of data; writing of the report; and the decision to submit the report for publication, including whether they will have ultimate authority over any of these activities	p. 26, 614-615	
Roles and responsibilities: committees	#5d	Composition, roles, and responsibilities of the coordinating centre, steering committee, endpoint adjudication committee, data management team, and other individuals or groups overseeing the trial, if applicable (see Item 21a for data monitoring committee)	p. 26, 612-621	
**Introduction**				
Background and rationale	#6a	Description of research question and justification for undertaking the trial, including summary of relevant studies (published and unpublished) examining benefits and harms for each intervention	p. 3-8	
Background and rationale: choice of comparators	#6b	Explanation for choice of comparators	p. 9, 201-204	
Objectives	#7	Specific objectives or hypotheses	p. 9, 201-204	
Trial design	#8	Description of trial design including type of trial (eg, parallel group, crossover, factorial, single group), allocation ratio, and framework (eg, superiority, equivalence, non-inferiority, exploratory)	p. 4-5, 204-207	
**Methods: Participants, interventions, and outcomes**				
Study setting	#9	Description of study settings (eg, community clinic, academic hospital) and list of countries where data will be collected. Reference to where list of study sites can be obtained	p. 14, 218-219	
Eligibility criteria	#10	Inclusion and exclusion criteria for participants. If applicable, eligibility criteria for study centres and individuals who will perform the interventions (eg, surgeons, psychotherapists)	p. 9, 221-224	
Interventions: description	#11	Interventions for each group with sufficient detail to allow replication, including how and when they will be administered	p. 11-16	
Interventions: modifications	#11b	Criteria for discontinuing or modifying allocated interventions for a given trial participant (eg, drug dose change in response to harms, participant request, or improving / worsening disease)	p. 10, 249-250	
Interventions: adherance	#11c	Strategies to improve adherence to intervention protocols, and any procedures for monitoring adherence (eg, drug tablet return; laboratory tests)	p. 10, 249-250; p. 13-14, 285-302	
Interventions: concomitant care	#11d	Relevant concomitant care and interventions that are permitted or prohibited during the trial		None, not monitoring any other care/interventions of participants
Outcomes	#12	Primary, secondary, and other outcomes, including the specific measurement variable (eg, systolic blood pressure), analysis metric (eg, change from baseline, final value, time to event), method of aggregation (eg, median, proportion), and time point for each outcome. Explanation of the clinical relevance of chosen efficacy and harm outcomes is strongly recommended	p. 15-17, 322-376	
Participant timeline	#13	Time schedule of enrolment, interventions (including any run-ins and washouts), assessments, and visits for participants. A schematic diagram is highly recommended (see Figure)	p. 14-15, 304-320; Fig. 1	
Sample size	#14	Estimated number of participants needed to achieve study objectives and how it was determined, including clinical and statistical assumptions supporting any sample size calculations	p. 11, 252-255; p. 16-17, 364-371	
Recruitment	#15	Strategies for achieving adequate participant enrolment to reach target sample size	p. 9-10, 218-250	
**Methods: Assignment of interventions (for controlled trials)**				
Allocation: sequence generation	#16a	Method of generating the allocation sequence (eg, computer-generated random numbers), and list of any factors for stratification. To reduce predictability of a random sequence, details of any planned restriction (eg, blocking) should be provided in a separate document that is unavailable to those who enrol participants or assign interventions	p. 14, 305-306	
Allocation concealment mechanism	#16b	Mechanism of implementing the allocation sequence (eg, central telephone; sequentially numbered, opaque, sealed envelopes), describing any steps to conceal the sequence until interventions are assigned	P. 9, 207-208	
Allocation: implementation	#16c	Who will generate the allocation sequence, who will enrol participants, and who will assign participants to interventions	p. 9, 209-210	
Blinding (masking)	#17a	Who will be blinded after assignment to interventions (eg, trial participants, care providers, outcome assessors, data analysts), and how	p. 9, 213-215	
Blinding (masking): emergency unblinding	#17b	If blinded, circumstances under which unblinding is permissible, and procedure for revealing a participant’s allocated intervention during the trial		Not applicable, since this is not a drug trial, there is no reason to reveal the intervention status during the trail
**Methods: Data collection, management, and analysis**				
Data collection plan	#18a	Plans for assessment and collection of outcome, baseline, and other trial data, including any related processes to promote data quality (eg, duplicate measurements, training of assessors) and a description of study instruments (eg, questionnaires, laboratory tests) along with their reliability and validity, if known. Reference to where data collection forms can be found, if not in the protocol	p. 13, 291-294; p. 15, 323-337; data collection forms are available upon request of the authors	
Data collection plan: retention	#18b	Plans to promote participant retention and complete follow-up, including list of any outcome data to be collected for participants who discontinue or deviate from intervention protocols	p. 10, 249-250; p. 13-14, 286-302	
Data management	#19	Plans for data entry, coding, security, and storage, including any related processes to promote data quality (eg, double data entry; range checks for data values). Reference to where details of data management procedures can be found, if not in the protocol	p. 17-19, 379-433; p. 20, 459-467	
Statistics: outcomes	#20a	Statistical methods for analysing primary and secondary outcomes. Reference to where other details of the statistical analysis plan can be found, if not in the protocol	p. 19-20, 435-457, Appendix 2	
Statistics: additional analyses	#20b	Methods for any additional analyses (eg, subgroup and adjusted analyses)	p. 19-20, 435-457, Appendix 2	
Statistics: analysis population and missing data	#20c	Definition of analysis population relating to protocol non-adherence (eg, as randomised analysis), and any statistical methods to handle missing data (eg, multiple imputation)	Appendix 2	
**Methods: Monitoring**				
Data monitoring: formal committee	#21a	Composition of data monitoring committee (DMC); summary of its role and reporting structure; statement of whether it is independent from the sponsor and competing interests; and reference to where further details about its charter can be found, if not in the protocol. Alternatively, an explanation of why a DMC is not needed	p. 20, 459-467	
Data monitoring: interim analysis	#21b	Description of any interim analyses and stopping guidelines, including who will have access to these interim results and make the final decision to terminate the trial		None, we will not be conducting interim analyses.
Harms	#22	Plans for collecting, assessing, reporting, and managing solicited and spontaneously reported adverse events and other unintended effects of trial interventions or trial conduct	p. 10, 238-249, Appendix 1	
Auditing	#23	Frequency and procedures for auditing trial conduct, if any, and whether the process will be independent from investigators and the sponsor	p. 21, 496-498	
**Ethics and dissemination**				
Research ethics approval	#24	Plans for seeking research ethics committee / institutional review board (REC / IRB) approval	p. 24-25, 582-590	
Protocol amendments	#25	Plans for communicating important protocol modifications (eg, changes to eligibility criteria, outcomes, analyses) to relevant parties (eg, investigators, REC / IRBs, trial participants, trial registries, journals, regulators)	p. 25, 587-588	
Consent or assent	#26a	Who will obtain informed consent or assent from potential trial participants or authorised surrogates, and how (see Item 32)	p. 9-10, 224-236, Appendix 1	
Consent or assent: ancillary studies	#26b	Additional consent provisions for collection and use of participant data and biological specimens in ancillary studies, if applicable	p. 9-10, 224-236, Appendix 1	
Confidentiality	#27	How personal information about potential and enrolled participants will be collected, shared, and maintained in order to protect confidentiality before, during, and after the trial	p. 20, 465-467	
Declaration of interests	#28	Financial and other competing interests for principal investigators for the overall trial and each study site	p. 26, 610-611	
Data access	#29	Statement of who will have access to the final trial dataset, and disclosure of contractual agreements that limit such access for investigators	p. 20, 465	
Ancillary and post trial care	#30	Provisions, if any, for ancillary and post-trial care, and for compensation to those who suffer harm from trial participation	p. 14, 300-302	
Dissemination policy: trial results	#31a	Plans for investigators and sponsor to communicate trial results to participants, healthcare professionals, the public, and other relevant groups (eg, via publication, reporting in results databases, or other data sharing arrangements), including any publication restrictions	p. 25, 597-607	
Dissemination policy: authorship	#31b	Authorship eligibility guidelines and any intended use of professional writers	p. 25, 597-607	
Dissemination policy: reproducible research	#31c	Plans, if any, for granting public access to the full protocol, participant-level dataset, and statistical code	p. 25, 597-607	
**Appendices**				
Informed consent materials	#32	Model consent form and other related documentation given to participants and authorised surrogates	Appendix 1	
Biological specimens	#33	Plans for collection, laboratory evaluation, and storage of biological specimens for genetic or molecular analysis in the current trial and for future use in ancillary studies, if applicable	Appendix 1	

## Methods

### Study design

This study is an ongoing collaboration between Million Marker and the Healthy Nevada Project (MM-HNP Study). We will test and compare the effectiveness of 1) EDC exposure report-back (control), and  2) a self-directed online interactive curriculum of EDC EHL material, with access to live coaches and an online forum (intervention). We hypothesize that the self-directed online interactive curriculum with personalized and community support will be more effective (superior) than EDC report-back alone at reducing EDC exposures (behavior change and metabolite concentrations), as well as increasing EDC-specific EHL, readiness to reduce exposures, and well-being. These two arms will be tested in a longitudinal EDC randomized control trial (n=600). Participants will be allocated to intervention groups by the MM team via block randomization, using random-number generation software. The HNP team will generate the allocation sequence and enroll participants. Outcomes for this aim will measure surveyed changes pre- post-interventions in EDC EHL, including EDC-specific knowledge/behavior/attitudes, RtC, well-being, and urine EDC metabolite concentrations. Additionally, we will test a subset of individuals from each intervention arm (*N* = 150 from each group, for a total of
*N* = 300) for clinical biomarkers using a mail-in blood card test. Outcome assessors and data analysts will be blinded to the intervention status of the participants. Additionally, participants will not be aware of their intervention status (i.e. what the other group undergoes).

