**Methods:**

We will test a self-directed online interactive curriculum with live counseling sessions and individualized support modeled after the highly effective Diabetes Prevention Program (DPP). Recruiting from the Healthy Nevada Project (HNP), one of the largest population health cohorts in the world, we test the effectiveness of our EDC-specific online intervention curriculum via EHL and RtC surveys and determine changes in EDC exposure before and after intervention in a randomized controlled trial. We will also test for common clinical biomarkers via a commercially available at-home test (Siphox). We will recruit and randomize 300 women and 300 men of reproductive age (total *n*=600) from HNP. Our target population is men and women of reproductive age (18–44 years old).

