### Sample size

We will recruit and randomize 600 participants (1:1 male to female). According to previously published research, this has the power to detect estimated effect sizes for 13 endpoints (9 metabolites and 3 survey analyses), [6, 44, 56, 60, 61] from a sample of *n* = 150 participants per arm (i.e., after 50% attrition down from the original *n* = 300 per arm).

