### Clinical biomarker testing

In addition to reducing EDC exposure via report-back/intervention programs, we will also assess clinical endpoints which may be improved by the reduction of EDC exposures as well as our lifestyle behavioral intervention program. To do this, we have partnered with SiPhox, a direct-to-consumer health and disease biomarker testing company [72]. SiPhox uses blood spot technologies to cost-effectively test a wide range of biomarkers involved in cardiovascular diseases and inflammation (apolipoprotein AI (Apo-AI), apolipoprotein B (ApoB), high-sensitivity C-reactive protein (hs-CRP), high-density lipoprotein (HDL), low-density lipoprotein (LDL), triglycerides (TG)), metabolic disease and diabetes (hemoglobin A1C (HbA1c), insulin), hormones and fertility (estradiol, testosterone, free testosterone, prostate-specific antigen, follicle-stimulating hormone (FSH), luteinizing hormone (LH), prolactin, sex-hormone binding globulin (SHBG), anti-Mullerian hormone, thyroid-stimulating hormone (TSH)), stress (cortisol, DHEA), and cancer (hs-CRP, prostate-specific antigen). These biomarkers can indicate risk for disease as well as the extent of ongoing disease states. Changes in these biomarkers can indicate improvement in health and reduced risk for disease. For example, high levels of high-sensitivity C-reactive protein (hs-CRP) indicates chronic inflammation and contributes to many diseases, including cancer, heart disease, lung disease, chronic obstructive pulmonary disease, chronic kidney disease, Alzheimer’s disease, diabetes, obesity, and high blood pressure. Thus reducing hs-CRP can reduce the risk for these diseases.^3^ Similarly, changes in hormone levels, such as increased testosterone, can indicate increased fertility and male reproductive health [73, 74].

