For the analysis plan, we will examine the distribution and concentrations of each of 13 chemical analytes in urine to determine geometric means, medians, percentiles and ranges of exposures. We will compare the percentiles with those reported in the NHANES study. We will include BMI, age, gender, diet, education and household income as covariates. Participants’ dietary patterns will be captured prior to sample collection by looking at their consumption of packaged food and times eating out as these are important culprits of EDC exposures. We will conduct an intent-to-treat analysis. The primary outcomes are the pre-post (first and second tests) differences in specific gravity-adjusted concentration levels per analyte. Clinical biomarkers measured before and after the intervention will also be compared to assess improvement in health and reduced disease risk. We willassess changes in participants’ EHL, RtC and well-being before and after the interventions as well. We will first generate summary statistics on participants’ responses. Changes will be calculated based on paired values of individual responses.

For all analyses, data will be reviewed to ensure assumptions are not violated. If outcomes are not sufficiently normally distributed for parametric tests to be valid, nonparametric tests will be conducted. If needed, variables with response categories with too few participants will be combined. Attrition analyses will be run to compare demographic variables between participants who completed post-test surveys and those who did not.

Summary data and associations between demographic variables and EHL, RtC, well being, EDC metabolites, and clinical biomarkers will be analyzed for all participants with pre-test survey data. Independent sample t-tests, one-way ANOVAs, Chi-square tests, and Spearman’s rank correlations will be run as appropriate. Changes from pre-test to post-test comparing differences between the intervention and control groups, will be analyzed for participants who completed both surveys using regression analyses, controlling for significant demographic variables.

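### The blood-test subset is sized on testosterone in men but counts all 150 participants per arm from a half-female trial; sex hormones need within-sex analysis and a restated power

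*Protocol article*

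**What the plan says.** **Sex mix.** The Sample size section states: "We will recruit and randomize 600 participants (1:1 male to female". The abstract gives the same split, 300 women and 300 men.

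**Allocation.** Under Study design, participants are assigned "via block randomization, using random-number generation software". No stratification factor is named.

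**Blood-test subset.** The Clinical biomarker testing section plans 150 individuals per arm and does not give their sex mix. The panel includes testosterone, free testosterone, estradiol, PSA, FSH, LH and anti-Mullerian hormone. On direction of benefit, it says that "increased testosterone, can indicate increased fertility and male reproductive health". The sample size takes an average effect of 0.37 from a meta-analysis of testosterone in men. With a two-tailed paired t-test, alpha 0.05 and 95% power it needs 97, multiplied by 1.3 for attrition to give 126 per group. It concludes that 150 per group is enough.

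**Arm comparison.** The Data collection, management, and analysis section lists sex or gender among the covariates in two places. It then describes the between-arm analysis of survey changes as "using regression analyses, controlling for significant demographic variables". No arm-by-sex term or by-sex arm estimate is stated.

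**Earlier study.** The Previous work section reports that "post-intervention, women increased their readiness (p=0.053), while men decreased (p=0.007".

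**The concern.** The calculation for free testosterone uses an effect seen in men, and then offers all 150 participants in the arm as the sample for it. In a trial that is half women, that works only if men and women are analysed together, or if the subset is nearly all men, which the article does not say.

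Pooling is a problem of meaning before it is one of power. The article reads a rise in testosterone as good news for men and gives no reading for women. A pooled mean change therefore has no agreed direction of benefit. The same holds for estradiol, FSH and LH, which the article lists without a direction for either sex. PSA and anti-Mullerian hormone are hard to read in a mixed group for the same reason.

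At stake is whether the hormone results, which the sponsor wants as evidence of health benefit, can be interpreted, and whether the stated 95% power applies to the men for whom the effect was estimated.

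**Working it through.** **1. Reproduce the plan's figure.** Inputs, all from Clinical biomarker testing: d = 0.37, two-sided alpha 0.05, power 95%, paired t-test. Power is P(|T| > t(0.975, n−1)), where T is noncentral t with n−1 degrees of freedom and noncentrality d√n.
- n = 96: power 0.948.
- n = 97: noncentrality 0.37 × √97 = 3.64; power 0.950. So 97 is correct.
- 97 × 1.3 = 126.1, given as 126; two groups give 252. Both agree with the text.

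**2. Count the men.** The sex mix of the subset is not stated. Assume it follows the trial's 1:1 quota: 150 × 0.5 = 75 men per arm. Undoing the plan's attrition factor gives 75 / 1.3 = 57.7, about 58 men.

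**3. Power for men at d = 0.37, same test.**

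| Men per arm | Noncentrality 0.37√n | Power |
|---|---|---|
| 97 (plan's requirement) | 3.64 | 0.95 |
| 75 (no attrition) | 3.20 | 0.89 |
| 58 (after factor 1.3) | 2.82 | 0.79 |

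The Sample size section allows 50% attrition for the main trial. If that applied to the subset, about 37 men would remain and power would be about 0.59.

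**4. What 95% power in men would need.** The plan's 126 per group would all have to be men. Each arm of 300 has about 300 × 0.5 = 150 men, so this is possible, but it would leave 150 − 126 = 24 places for women in the subset.

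**5. Blocks within sex.** With 300 men among 600 and 300 per arm, the number of men in an arm has SD √(300 × 0.25 × 300/599) = 6.1 under unrestricted allocation. The 95% range is 138 to 162. The imbalance is small, and a sex covariate can adjust for it.

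**6. By-sex estimates for readiness to change.** Take 150 completers per arm (the plan's 50% attrition) and equal attrition by sex (assumption), so 75 per sex per arm. In SD units the arm-by-sex difference has standard error √(4/75) = 0.231. The difference detectable at 80% power is (1.960 + 0.842) × 0.231 = 0.65 SD. The arm effect within one sex is detectable at (1.960 + 0.842) × √(2/75) = 0.46 SD.

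**The case against.** The strongest reply is that nothing in the article says these hormones will be pooled. The analysis text says only that biomarkers before and after will be compared, Expected outcomes and limitations calls the biomarker work exploratory, and linking testosterone to male health may mean that a within-sex analysis is intended. That is fair as far as intention goes. It does not rescue the sample size statement. If the analysis is within sex, 150 is not the number available for free testosterone, and the stated power is too high.

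It is also fair that strata and subgroup analyses may be set out elsewhere: the SPIRIT checklist sends additional analyses to Appendix 2, which is not shown. So the article's silence on sex strata or an arm-by-sex term is not evidence that they are absent, and those items are requests to confirm or add.

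A reader might infer something stronger: that because readiness rose in women and fell in men, opposite arm effects will cancel in a pooled comparison under a 1:1 quota. The documents do not support this. The earlier pattern is a before-after change following report-back, and Intervention design gives report-back to both arms. A pattern shared by both arms subtracts out of the arm difference. Effects of +0.37 and −0.37 SD would average to zero, but no passage suggests that curriculum versus report-back acts that way, and the women's result was p=0.053. Nor would unstratified blocks cause cancellation; they affect balance and precision only. Readiness is also not a primary outcome.

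**Conclusion.** The point holds for the sex hormones. The subset calculation applies an effect from men to a count that, in a 1:1 trial, would include women, and a pooled comparison of these markers has no single interpretation. For men alone, power is about 0.89 with 75 per arm and 0.79 with 58, against the stated 0.95. These figures assume a 1:1 subset, the plan's effect of 0.37, and its paired within-group test.

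The matter is minor for the trial as a whole, because the primary outcomes are urinary analytes and the biomarkers are exploratory. The remaining sex-related items are small improvements. The article is not consistent on whether sex is always in the arm-comparison model, since it is listed as a covariate but that model controls only for significant demographic variables. No cancellation of arm effects on readiness to change has been shown.

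**What to change.** 1. Draw the 150-per-arm blood-test subset at random within sex, and state the numbers of men and women.
2. Analyse testosterone, free testosterone, estradiol, FSH, LH, PSA and anti-Mullerian hormone within sex only, stating the expected direction of benefit for each sex in which the marker is analysed.
3. Restate the power for men: about 0.89 with 75 and 0.79 with 58 if the subset is 1:1. If 95% is wanted, the subset needs about 126 men per arm.
4. Minor additions: form the blocks within sex in the remaining recruitment waves; keep sex in the arm-comparison model whether or not it is significant; and report the arm effect on readiness to change in each sex as a secondary estimate, noting that only an arm-by-sex difference of about 0.65 SD is detectable at 80% power. If Appendix 2 already covers these, a cross-reference is enough.

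The cost is a sampling rule, a randomisation setting for later waves, one model term and a few sentences. The main drawback is that each within-sex hormone estimate uses about half the subset. Raising the number of men to 126 per arm would restore the stated power but leave few places for women.
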